**Figure 1: Schema of Study Design for the Evaluation of FAM-CARE Program Design:**

**Four clusters of Health Care Facilities/Clinics in Hhohho Region Swaziland**

**Two hospital-based clusters with their filter clinics & two health center-based clusters with their filter clinics**

**Random selection of clusters** **(stratified by whether health center vs hospital cluster) to implement** **family-centered model of care or continue standard care**

**Randomized**

**Cluster Selection for Implementation**

| **Control Standard of HIV Care Continued**  *Dvokolwako Health Center cluster*  Four filter clinics  *Mbabane Hospital cluster*  Twelve filter clinics |
| --- |

| **Family Centered Care Model Implementation**  *Emkhuzweni Health Center cluster*  Three filter clinics  *Pigg’s Peak Hospital cluster*  Ten filter clinics |
| --- |

**Prospective study enrollment**

Will be done within the randomized hospital or health center

“parent” of the cluster plus the largest filter clinic in the cluster

| **Study Arm 1 Cohort Enrollment**  **(Intervention - Family-Center Care)**  **Emkhuzweni Health Center**  **Mangweni Clinic**  **Pigg’s Peak Hospital**  **Horo Clinic** |
| --- |

| **Study Arm 2 Cohort Enrollment**  **(Control – Standard HIV Care)**  **Dvokolwako Health Center**  **Balekane Nazarene Clinic**  **Mbabane Hospital**  **Lobamba ART Clinic** |
| --- |

**Enroll**

**HIV-positive child <15 years**

- **Receiving ART (endoints: viral suppression/HIV RNA >1,000 c/mL; pattern of retention)**
- **Not receiving ART (endoints: ART initiation; viral suppression /HIV RNA >1,000 c/mL; patterns of retention)**

**Follow-up: 18 months**

**Enroll**

**HIV-positive child <15 years**

- **Receiving ART (endoints: viral suppression/HIV RNA >1,000 c/mL; pattern of retention)**
- **Not receiving ART (endoints: ART initiation; viral suppression /HIV RNA >1,000 c/mL; patterns of retention)**

**Follow-up: 18 months**

Our primary endpoints of viral suppression and HIV RNA >1,000 copies/mL will be evaluated among HIV-positive children entering the study who are initiating or receiving ART. The sample size will be powered to detect a difference in viral suppression/HIV RNA >1,000 copies/mL in children receiving ART in the FAM-CARE sites to those receiving ART in control sites. For HIV-positive children entering the study who are not currently on ART, we will be able to compare retention in care and the proportion of children initiating ART between those enrolled in the FAM-CARE sites to those in control sites.

At FAM-CARE sites, it is estimated that 10-20% of HIV-positive children may not be enrolled in the FAM-CARE program, because of disclosure or other issues within the family. These children will still be enrolled in the prospective cohort as long as there is >1 family member who is also HIV-positive; we will be able to compare suppression/ART failure/retention rates between children in FAM-CARE sites enrolled in the FAM-CARE program and not enrolled in the FAM-CARE program, although the study will not be powered based on this comparison. We will also be able to compare overall rates of viral suppression/HIV RNA >1,000 copies/mL among all children (regardless of actual participation in FAM-CARE programs) seen at facilities with the FAM-CARE program to those in control facilities.

An individual family may have more than one HIV-positive child, and more than one HIV-positive child that is receiving treatment; based on a review of pediatric enrollment at two sites, it is estimated that ~15% of HIV-positive children come from families with more than one child receiving ART. Viral suppression rates in children from families with more than one child on treatment may be correlated, particularly in the FAM-CARE program. We will create a “family identification number” that will be used at both FAM-CARE and control sites to identify children enrolled in the study who come from the same family, which will allow controlling for potential correlation during analysis.

We will enroll all HIV-positive children with >1 family member who is also HIV-positive seen at the study facilities until we have achieved the desired sample size total of 444 HIV-positive children from unique families receiving ART at enrollment (see *Statistical Methods*). We estimate we will need to enroll approximately 666 HIV-positive children into the study (333 per arm) to achieve the target sample size of 444 HIV-positive children receiving ART from unique families (222 per arm).

***Entry Criteria for Enrollment***

*Inclusion:*

- HIV-positive child aged <15 years receiving HIV care at the study facility.
  - At least one family member residing in the household is also HIV-positive and is receiving services at the study facility.

*Exclusion:*

- HIV-positive child attending care at study facility only temporarily.
- HIV-positive child with no other HIV-positive family members in household receiving services at the study facility.
- Significant medical condition in caregiver or child that would preclude active study participation.

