SOAR partner Elizabeth Glaser Pediatric AIDS Foundation (EGPAF) proposes to leverage existing and planned service delivery platforms in Swaziland to evaluate a model of care to improve pediatric retention and ART adherence. In the family-centered care (FAM-CARE) program, after identification of HIV infection in a child, active HIV testing of all family members is conducted and all HIV-positive family members are seen together as a unit and receive their care together. EGPAF-Swaziland is in the process of establishing a FAM-CARE service delivery program in selected health facilities in the Hhohho region of Swaziland, and roll-out of these services will provide a platform for this study. Viral load monitoring is in process of national roll-out in Swaziland. The planned study is an implementation science study to evaluate the implementation of the FAM-CARE program in Swaziland and its effect on viral suppression and retention in children living with HIV.

The proposed study will evaluate the effect of implementing a FAM-CARE program on viral suppression and retention in children through enrollment of a prospective cohort of HIV-positive children and their caregivers at sites implementing the FAM-CARE program and control sites continuing the current standard of care. The study will be conducted in four “clusters” of facilities (2 hospitals and 2 health centers and their filter clinics) in the Hhohho region of Swaziland. Two facility “clusters” (one hospital and one health center, with their filter clinics) will be randomized to initiate the FAM-CARE program with viral load monitoring and two “clusters” (one hospital and one health center, with their filter clinics) will be control standard-of care sites. A prospective cohort of HIV-positive children and their caregivers will be followed in the FAM-CARE program sites and control sites. Each child will be followed for 18 months following enrollment. The primary objective is to evaluate the effect of the FAM-CARE program on the rates of viral suppression and retention in care, comparing rates of viral suppression and retention in children enrolled in FAM-CARE vs control sites. The study will also evaluate factors associated with viral suppression and retention (including family demographic characteristics), and conduct qualitative interviews to assess the acceptability of the FAM-CARE program by caregivers and health care providers in the intervention sites.

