***Description of FAM-CARE Service Program***

EGPAF-Swaziland is piloting a FAM-CARE program, implemented with program funding prior to initiation of the current study. Viral load monitoring is in the process of being implemented at all HIV care sites in Swaziland. For implementation of the FAM-CARE program, EGPAF-Swaziland has randomly selected one hospital and one health center and its cluster clinics (Emkhuzweni cluster and Pigg’s Peak cluster) as FAM-CARE sites and one hospital and one health center and its filter clinics (Dvokolwako cluster and Mbabane cluster) which continue their current standard of HIV care (separate pediatric and adult HIV clinics) and serve as control comparison sites. A brief description of the FAM-CARE program that has been implemented at the selected sites is provided below.

*Enrollment of patients into the FAM-CARE program*

Children receiving HIV care and treatment services at the selected FAM-CARE facilities will be the primary starting point for identifying other HIV-positive family members to be enrolled into care. The children will be recruited primarily from the HIV care and treatment departments, and in any other units within the health facility such as maternal/child health programs or PMTCT follow-up programs. After identifying a child receiving HIV treatment services, the health care worker will talk to the mother or caregiver about the FAM-CARE program within the health facility.

The adult who has brought the child to the facility will be asked the following questions:

1. If they are also HIV-positive and receiving care and treatment services. If yes, they would be invited to participate in the FAM-CARE initiative at the facility.
2. If any of their family members (spouse, children etc.) are also HIV-positive and receiving care and treatments services. If yes, an invitation letter will be issued inviting all family members to come to the health facility to participate in the FAM-CARE program at the facility if feasible. If needed, the facility health care workers will facilitate transfer out from other facilities for family members receiving HIV care at another facility. Even if the family members are not on ART but are known to be HIV-positive, they will be invited to participate in the FAM-CARE program.

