3. If any of their family members (spouse, children etc.) have not tested for HIV in the past year. If yes, an invitation letter will be issued inviting all family members to come to the health facility for HIV testing. If any member is found HIV-positive, s/he would be invited to participate in the FAM-CARE program at the facility

Additionally, HIV-positive adults receiving care and treatment services will also be used as index cases to identify HIV-positive children for enrollment into the FAM-CARE program. Each family should have at least one HIV-positive child receiving HIV treatment services.

*Eligibility criteria for enrollment into FAM-CARE program*

- Presence of at least one child (up to the age of 15 years) who is HIV-positive and receiving care at the selected facility. A child will be enrolled if newly diagnosed as HIV-positive and not yet on ART (ART-naïve) or if already known to be HIV-positive but not yet initiated treatment (ART-naïve) or if already on treatment (ART-experienced).
- Family members (someone who is related to the child either by blood or adoption. These can include the mother, father, sister(s) and brother(s), cousins) receiving HIV care and treatment services and residing in the same household as the index child.
- Willingness to disclose HIV status to other family members.

It is estimated that the majority of HIV-positive children will have an HIV-positive family member, but a small percentage may be orphans cared for in a household without other HIV-positive children or adults. Additionally, a small percentage of mothers may not want to participate in the family-centered program because of disclosure issues. We estimate that this will not be more than 10-20% of HIV-positive children. These children would continue their care at the intervention facility but outside of the FAM-CARE program (e.g., routine pediatric or adult HIV clinics).

*Provision of FAM-CARE services*

All family members will be registered in the health facility as a family unit and will have their chronic care files kept in one family folder. Appointments for HIV care and treatment services will be made on the same day for the family as a unit. It is standard for HIV-positive pediatric patients on ART to be seen for monthly visits and ART pick-up. Decisions regarding ART initiation will be based on Swaziland national treatment guidelines.

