We will enroll a prospective cohort of HIV-positive children <15 years with at least one additional HIV-positive family member in the household from FAM-CARE and control sites to evaluate the effect of the FAM-CARE program on viral suppression, HIV RNA level >1,000 copies/mL, and retention in care (See **Figure 1**). All HIV-positive children in clinical care, regardless of treatment status or enrollment in the FAM-CARE program, are eligible for enrollment into the study if there is at least one additional HIV-positive family member residing in the household. It is estimated that 85-90% of children in HIV care are currently receiving ART.

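### Eligibility depends on a relative's care at the study facility, which FAM-CARE can itself bring about, so who may enter the cohort can depend on arm

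*Protocol*

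**What the plan says.** Entry Criteria for Enrollment sets the condition twice. The inclusion criterion is "At least one family member residing in the household is also HIV-positive and is receiving services at the study facility". The exclusion mirrors it: "HIV-positive child with no other HIV-positive family members in household receiving services at the study facility".

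Other sections state a looser rule. Subject Population (below Table 2) says that all HIV-positive children in care "are eligible for enrollment into the study if there is at least one additional HIV-positive family member residing in the household", whatever their treatment status or participation in FAM-CARE. Later in the same section, children at FAM-CARE sites who are outside the programme are still to be enrolled provided another family member is HIV-positive. Recruitment also asks only for an additional HIV-positive relative in the household. None of these requires the relative to attend the study facility.

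Description of FAM-CARE Service Program says the programme was implemented before the study began. For relatives treated elsewhere: "If needed, the facility health care workers will facilitate transfer out from other facilities for family members receiving HIV care at another facility". For relatives not tested in the past year: "If yes, an invitation letter will be issued inviting all family members to come to the health facility for HIV testing", and those found positive are invited into the programme. HIV-positive adults also serve as index cases for finding children. The Summary of Proposed Research describes the model as one in which "active HIV testing of all family members is conducted". Control sites continue with separate pediatric and adult clinics, and no family testing or transfer step is described for them.

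**The concern.** Clusters were randomised before children were enrolled. A criterion applied afterwards keeps the arms comparable only if allocation cannot change whether a child meets it. Here it can. A child whose mother is in care elsewhere may become eligible at a FAM-CARE site once she transfers, while a similar child at a control site stays ineligible. A child whose parent is untested may become eligible once the programme tests that parent.

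The status may also be prognostic. The Background cites loss to follow-up of 19% in women without a co-enrolled HIV-positive relative, against 3-8% in those with one. That evidence concerns women rather than children, but the protocol uses it to motivate the model. If shared care at one facility goes with better outcomes, a rule that admits different families by arm can shift the contrast in viral suppression without any programme effect. Separately, sites cannot apply both versions of the eligibility rule.

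**Working it through.** **Does eligibility depend on arm?** Three passages settle it.

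1. Entry Criteria: the relative must be receiving services at the study facility.
2. Description of FAM-CARE Service Program: the programme transfers relatives in and tests them at the facility, and it started before enrolment.
3. Same section, control sites: standard care continues, with no equivalent step described.

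The programme therefore acts on the criterion before it is judged, in one arm only as far as the text goes.

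**Do the planned analyses deal with it?** The protocol's Statistical Analysis Plan section offers four things.

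- Baseline characteristics are compared by arm, and the model adjusts for imbalances in children's characteristics. This helps for measured differences. It cannot bring in control children who were never eligible.
- The propensity score models accepting versus declining FAM-CARE, using FAM-CARE sites only. It does not address who became eligible.
- The intent-to-treat comparison covers all children at each type of facility. The Confidentiality section says data on non-participants are not collected, so in practice it is limited to enrolled children and carries the same selection.
- Multilevel models handle correlation by family and facility, not selection.

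**The plan's own figure.** For 80% versus 90% suppression, two-sided alpha 0.05, power 80%:

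n = [1.960 × √(2 × 0.85 × 0.15) + 0.842 × √(0.80 × 0.20 + 0.90 × 0.10)]² / 0.10² = 199 per arm, 398 in total. With 10% loss, 199 / 0.90 rounds up to 222 per arm, 444 in total. Table 3 reproduces exactly and is not in dispute.

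**Possible size.** The documents give no inputs, so these are assumptions. Let s be the share of FAM-CARE enrollees who qualify only through programme transfer or testing, and d the difference between their suppression and that of the rest. Suppose the remaining FAM-CARE enrollees resemble control enrollees, with suppression p. With no true effect, suppression in the FAM-CARE arm is (1 − s)p + s(p + d) = p + s·d, so the contrast shifts by s·d.

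- s = 0.10, |d| = 0.05: 0.005, or 0.5 points.
- s = 0.30, |d| = 0.15: 0.045, or 4.5 points, which is 45% of the 10-point target.

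The table shows the effect on the unadjusted chi-square test, with 80% control suppression, 199 analysed per arm and no within-facility correlation (the protocol's own sample-size assumption). Without selection, the figures are 5% rejection and 80.0% power.

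| s | d (points) | Shift (points) | Rejection rate, no true effect | Power, true effect +10 points |
|---|---|---|---|---|
| 10% | −10 | −1 | 5.7% | 70.0% |
| 10% | +10 | +1 | 5.7% | 87.9% |
| 20% | −10 | −2 | 7.8% | 58.6% |
| 20% | +10 | +2 | 8.0% | 93.5% |
| 30% | −10 | −3 | 11.2% | 46.8% |
| 30% | +10 | +3 | 12.0% | 96.9% |

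Higher power in the positive rows is not a gain, since it comes from bias.

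**The case against.** The strongest reply is that nothing in the protocol shows the enrolled families actually differ. It does not say how often relatives attend elsewhere, how many transfer, or how many are first diagnosed through the programme. At many sites the same nurse sees adults and children, and the sponsor supports testing and treatment at 38 of the 41 public facilities in the region, across both arms. Shared care and testing of relatives can therefore arise under standard care. This stands. A reader might infer that the arms are demonstrably non-comparable, or that control families are limited to those who chose to attend together. The documents support neither. They support only that eligibility can depend on arm.

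Second, baseline viral load, ART history and family HIV history are collected in both arms and could feed the planned adjustment. This too stands, as a partial remedy: adjustment works only among children who entered.

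Third, the criterion has a purpose. It matches FAM-CARE's own requirement that relatives receive HIV services, and it eases abstraction of relatives' records for the family factors in secondary objective 2. That is a genuine cost of dropping it. However, Recruitment and Study Procedures both say that a relative's consent to abstraction is not needed to enrol a child.

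Fourth, dropping the facility condition does not close the testing route, because a relative must still be known to be HIV-positive. This is correct, and the fix has to cover it.

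**Conclusion.** The point holds in a limited form. The entry criteria conflict with Subject Population and Recruitment, and the stricter version rests on a status that FAM-CARE can produce before eligibility is judged, with no matching step described at control sites. The arms can be expected to recruit different families, and the planned analyses repair this only in part.

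The documents fix neither the size nor the direction of any bias. The range of 0.5-4.5 points either way rests wholly on the assumed 10-30% share and 5-15 point difference, before any covariate adjustment. Its upper end combines the extremes of both ranges and should not be read as an estimate. A reader might also infer that the bias favours one arm, but nothing in the protocol settles that. The sample-size figures are unaffected.

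**What to change.** Remove the condition that the relative receive services at the study facility from both the inclusion and the exclusion criterion, so that they agree with Subject Population and Recruitment. This closes the transfer route.

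In both arms, record at enrolment whether the qualifying relative was already known to be HIV-positive before the FAM-CARE launch date, and where that relative was then in care. Repeat the primary analysis, with the same restriction in both arms, in children whose relative was known to be HIV-positive before launch. This covers relatives found by programme testing. If the sponsor keeps the facility condition, restrict the repeat analysis further to children whose relative already attended the study facility before launch.

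The cost is a protocol amendment to one paired criterion, two added enrolment items and one sensitivity analysis. Some relatives' clinic records will lie at other facilities, which reduces the family-factor data for secondary objective 2, and the sensitivity set will be smaller than the main analysis set.

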***Recruitment***

Eligible HIV-positive children age <15 years and their caregivers from families with at least one additional HIV-positive family member residing in the household at study sites will be identified and referred by clinic staff to the site study nurse, who will explain the study and study procedures. The study nurse will conduct the informed consent procedures with eligible caregivers and informed assent discussion with older children (> 12 years to <15 years) in a private location with a witness present in the case of an illiterate participant. The informed consent form (and informed assent form when relevant) will be read to the caregiver/child and h/she will be given the opportunity to ask questions. Written informed consent will be obtained from the mother/caregiver prior to any study procedures being conducted. Mothers under the age of 18 years will be treated as mature (emancipated) minors and able to provide informed consent for themselves and their children. After obtaining written informed consent from the caregiver, the study nurse will seek verbal informed assent from children >12 to <15 years of age. Once informed consent (and informed assent as appropriate) are obtained, participants will be enrolled in the study and assigned a participant study identification number that will include a family identification designation for all enrolled family members. Enrollment will continue in each site until the targeted number of HIV-positive children have been enrolled.

Informed consent will be sought from other HIV-positive adult (>18 years) family members at both FAM-CARE and control sites for abstraction of HIV-related clinical and laboratory data from medical records. For HIV-positive adolescents between the ages of 15 through 17 years, informed consent for data abstraction from existing medical records will be obtained from the mother/caregiver. However, this will not be required to enroll a child into the study. HIV-positive adults in the family who provide informed consent will be assigned a participant study identification number that includes a family study identification designation.

*Statistical Methodology*

*Sample size estimation*

The primary study endpoints are the proportion of children on ART with viral suppression (defined as HIV RNA below the level of assay detection) and the proportion with HIV RNA >1,000 copies/mL at 18 months. The tables below show the minimum number of children receiving ART needed to demonstrate significant (0.05) effects of the FAM-CARE program on viral suppression and HIV RNA >1,000 copies/mL compared to control facility care, assuming different viral suppression and HIV RNA >1,000 copies/mL rates in the control group.

**Table 3** (viral suppression) shows the minimum sample size per arm and overall needed to demonstrate a significant FAM-CARE program effect with 80% power at 5% significance levels, assuming different levels of viral suppression in children on ART from control facilities (ranging between 65-85% suppression) and different levels of improvement that could be observed in children in FAM-CARE program sites compared to control sites. With 398 HIV-positive children receiving ART from unique families, we will have 80% power to detect at least a 10% increase in viral suppression with FAM-CARE, assuming a viral suppression rate between 65% and 80% in control children on ART.

**Table 3.** Sample size estimates for detecting FAM-CARE effects on viral suppression rates

| % Viral Suppression in Control | Minimum Effect of FAM-CARE | % Viral Suppression in FAM-CARE Sites | Alpha | Power | Sample size/ arm | Total sample size | Adjusted for 10% LTFU |
| --- | --- | --- | --- | --- | --- | --- | --- |
| .65 | .15 | .80 | .05 | 80% | 138 | 276 | 308 |
| .65 | .20 | .85 | .05 | 80% | 73 | 146 | 164 |
| .65 | .25 | .90 | .05 | 80% | 43 | 86 | 96 |
| .70 | .15 | .85 | .05 | 80% | 121 | 242 | 270 |
| .70 | .20 | .90 | .05 | 80% | 62 | 124 | 138 |
| .75 | .15 | .90 | .05 | 80% | 100 | 200 | 224 |
| .80 | .10 | .90 | .05 | 80% | 199 | 398 | 444 |
| .85 | .05 | .90 | .05 | 80% | 686 | 1372 | 1526 |

**Table 4** (HIV RNA >1,000 copies/mL) shows the minimum number of children required to detect at least a 5%, 10%, or 15% improvement with FAM-CARE care sites compared to control sites, with 80% power at 0.05 significance level, assuming different HIV RNA >1,000 copies/mL rates in control children (ranging from 10-30%).

**Table 4:** Sample size estimates for detecting FAM-CARE effects on HIV RNA >1,000 c/mL

| % HIV RNA >1,000 c/mL in Control | Minimum Effect of FAM-CARE | % HIV RNA >1,000 c/mL in FAM-CARE Sites | Alpha | Power | Sample size/ arm | Total sample size | Adjusted for 10% LTFP |
| --- | --- | --- | --- | --- | --- | --- | --- |
| .10 | -.05 | .05 | .05 | 80% | 435 | 870 | 968 |
| .15 | -.05 | .10 | .05 | 80% | 686 | 1372 | 1526 |
| .15 | -.10 | .05 | .05 | 80% | 141 | 282 | 314 |
| .20 | -.05 | .15 | .05 | 80% | 906 | 1812 | 2014 |
| .20 | -.10 | .10 | .05 | 80% | 199 | 398 | 444 |
| .20 | -.15 | .05 | .05 | 80% | 76 | 152 | 170 |
| .25 | -.10 | .15 | .05 | 80% | 250 | 500 | 556 |
| .25 | -.15 | .10 | .05 | 80% | 100 | 200 | 244 |
| .30 | -.10 | .20 | .05 | 80% | 294 | 588 | 654 |
| .30 | -.15 | .15 | .05 | 80% | 121 | 242 | 270 |

We have adjusted the effective sample size to account for a possible 10% loss to follow up over the 18-month study period. Our estimation assumes enrolment of one HIV-positive child on ART per household and that there is no correlation of children’s viral load outcomes within facilities.

Assuming 10% loss to follow-up, we plan to enroll 444 HIV-positive children receiving ART from unique family units into the study over 12 months. With this sample size, we have power to detect a minimum of 10% increase from an estimated proportion of viral suppression of 80% in the control sites to 90% in the FAM-CARE sites or 15% increase in viral suppression with FAM-CARE if control rate of suppression is 75% or lower (Table 3 highlighted rows) and a minimum reduction in HIV RNA >1,000 copies/mL rates from 20% in the control sites to 10% in the FAM-CARE sites or from 15% in the control sites to 5% in the FAM-CARE sites (Table 4 highlighted rows).

*Study sampling procedures*

In both intervention and control facilities, all HIV-positive children under 15 years of age will be enrolled into the study until the number of target “family units” as per sample size calculation is achieved. A “family unit” is defined as a family in which at least one child <15 years enrolled in the study is receiving ART and has at least one additional family member who is HIV-positive. In the majority of instances, a family will have only one HIV-positive child on ART, and the family “unit” equals one enrolled child. However, if a family (in FAM-CARE or control sites) has more than one HIV-positive child on ART, all children on ART are enrolled, but for sample size purposes, this will equal one enrolled “family unit”. Data from all enrolled children will be included in the analysis with adjustment potential correlations due to family units (see analysis plan).

HIV-positive children initiating or receiving ART at study entry will contribute to the endpoints related to viral suppression and HIV RNA >1,000 copies/mL. HIV-positive children who are not receiving ART at study entry will contribute to endpoints related to retention in care and proportion of children not on ART who initiate ART during the study.

Assuming a 20% refusal of entry into FAM-CARE, that 15% of families will have more than one HIV-positive child enrolled in the study, and 15% of children will not be receiving ART at study entry, we estimate we will need to enroll approximately 666 HIV-positive children into the study (333 per arm) to achieve the target sample size of 444 HIV-positive children receiving ART from unique families.

